#### Methods

In a three-arm randomized controlled trial, older adults in Hong Kong who live alone and under the poverty line, do not have Internet at home, and feel lonely will be randomly assigned to receive one of the three interventions (enrollment goal,  $N = 966$ ). The primary outcomes will be loneliness, social network indicators and perceived social support. Secondary outcomes will be perceived stress, sleep quality, anxiety and depressive symptoms, physical and cognitive health. Underlying mechanisms will be examined with mindfulness, activity happiness/meaningfulness, diurnal cortisol patterns, levels of the salivary C Reactive Protein, and genetic markers (candidate gene, GWAS, biological pathway related SNPs, and polygenic risk scores).

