### Randomization

After completing baseline assessment, participants are randomly assigned to either Tele-BA, Tele-MF, or Tele-BF using an online random number generated by a research assistant. Participants are then informed of their assigned intervention, and Tele-BA participants receive copies of BA worksheets. Due to the nature of the intervention, participants cannot be blinded as the types of activities in each intervention group are distinct.

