## Supplement 1. Study Protocol

**Biomarkers.** One third of participants in the sample will be invited to provide saliva samples. After providing detailed guidelines in saliva sample collection, three saliva samples are collected by the participants using Salivette tubes at the participants' homes on 2 consecutive weekdays, three times each day: after waking up, before lunch, and before bedtime, 4 time points (baseline, 4-week, 3-month and 6-month follow-up). Standard instruction procedures and a telephone reminder are provided to participants. The collected Salivette tubes are kept frozen, and the cortisol levels are determined according to the manufacturer's standard using an ELISA kit (Salimetrics, PA, USA). Each participant's diurnal cortisol pattern is identified using four indicators: (1) morning cortisol, (2) evening cortisol, (3) mean cortisol, and (4) the diurnal cortisol slope. Salivary samples are also tested for CRP using the Salivary C-Reactive Protein ELISA kit according to the manufacturer's recommended protocol (Salimetrics, PA, USA).

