**Genotyping.** DNA is collected from saliva samples at baseline, and the Infinium OmniZhongHua-8 v1.3 BeadChip with 887,270 SNPs are used, as this type of chip has been widely used for genotyping in Chinese populations. This type of chip is designed to pay particular attention to alleles found in Chinese populations and is the best choice in terms of study design and cost. It covers common, intermediate, and rare variants found in Chinese populations for genome-wide association studies (GWAS). According to the manufacturer's information, it covers 77% of common variants (minor allele frequency [MAF] > 5%), 73% of intermediate variants (MAF > 2.5%), and 65% of rare variants (MAF > 1%) in Chinese populations at  $r^2 \geq 0.8$ . The assay has exceptionally high data quality in terms of call rates (average > 99%), reproducibility (> 99.9%), and low sample repeat rates, and has high signal-to-noise ratios and low overall noise levels, enabling accurate and reliable calls and copy number analysis. The Sequenom platform is used in the second stage of variant genotyping. The Sequenom system is based on single-base extension (SBE) chemistry and mass spectroscopy, and allows SNPs to be designed for 40-plex assays. If it is necessary to sequence candidate genes, mutation screening is conducted by direct sequencing of exons, intron-exon boundaries, and conserved promoter elements using the ABI 3730XL sequencer in the CGS HKU genotyping core facility. Thus, candidate genes, GWAS, polygenic risk scores, and SNPs from underlying biological pathways are used as genetic dispositions.

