#### Planned Analysis of the Effects of the Intervention

The effects of the intervention on loneliness are assessed using mixed models for repeated measures. Specifically, a conditional growth model analysis with an unstructured covariance matrix is conducted using a Group (two intervention groups and one control group)  $\times$  Time (baseline, 4 weeks, and 3-, 6-, and 12-month follow-ups) interaction as an indicator of the intervention effects. For sensitivity analysis, a similar mixed model for repeated measures with an unstructured covariance matrix, but with the ANOVA model, is used. The demographic characteristics that show significant differences across groups at baseline are controlled for in the models. In addition, an “intention-to-treat” analysis is used to assess differences in outcomes by incorporating participants who do not complete the study. The intention-to-treat principle is also applied, and all statistical analyses are conducted using SPSS 28. In order to test the effect of the proposed mediators, path analyses with manifest variables will be run with indirect effect specified and tested with 95% bias-corrected confidence intervals resulting from 1000 bootstraps in Mplus 8. Mindfulness, happy/meaningful events, CRP, the position of candidate genes, polygenic risk scores and SNPs are potential mediators to be tested.

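### Candidate genes, SNPs and polygenic scores are listed as mediators, but inherited genotype is fixed before randomisation, so every genetic indirect effect is zero by design

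*Protocol*

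**What the plan says.** Under Planned Analysis of the Effects of the Intervention, the protocol states that "path analyses with manifest variables will be run with indirect effect specified and tested with 95% bias-corrected confidence intervals". The same paragraph ends by naming the variables: "Mindfulness, happy/meaningful events, CRP, the position of candidate genes, polygenic risk scores and SNPs are potential mediators to be tested". The genetic variables thus have the same role and the same test as mindfulness, events and CRP.

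The placement elsewhere agrees. The Genotyping paragraph falls under the Mediators heading, and the abstract's Methods section includes genetic markers among the mechanisms to be examined.

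Other parts of the protocol describe these variables differently:

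- Genotyping, on timing: "DNA is collected from saliva samples at baseline".
- Genotyping, on role: "Thus, candidate genes, GWAS, polygenic risk scores, and SNPs from underlying biological pathways are used as genetic dispositions".
- Randomization, on allocation: "After completing baseline assessment, participants are randomly assigned to either Tele-BA, Tele-MF, or Tele-BF".

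On the other biological markers, the abstract says "Underlying mechanisms will be examined with mindfulness, activity happiness/meaningfulness, diurnal cortisol patterns", and the Biomarkers paragraph defines four cortisol indicators alongside salivary CRP. The closing mediator list names CRP but not cortisol.

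**The concern.** A mediator lies on the causal path from treatment to outcome, so the treatment must be able to change it. Eight telephone sessions cannot change a participant's inherited alleles, or a score computed from them. A genetic variable can bear on this trial in other ways: it may predict loneliness, or it may mark people who respond better or worse to an intervention. The first is a covariate role and the second an effect-modifier role. Neither is estimated by an indirect effect.

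What is at stake is how the mechanistic results are read. The protocol's Discussion presents biological mechanisms as one of the things the trial will test. A genetic indirect effect whose interval excludes zero would look like evidence of such a mechanism, although it could only be an accident of allocation.

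**Working it through.** The plan gives no figure on this point, so there is none to reproduce. The check has a logical part and a numerical illustration.

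**Logic.** For arm X, mediator M and outcome Y, the path model is:

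- M = i₁ + aX + e₁
- Y = i₂ + c′X + bM + e₂
- indirect effect = a × b

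Here a is the effect of the randomised arm on M. With three arms there are two such coefficients, one for each comparison with befriending.

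1. Genotype is measured at baseline (Genotyping) and allocation comes afterwards (Randomization).
2. Genotype would not change after allocation in any case.
3. Randomisation makes arm independent of anything fixed beforehand, so a = 0 for both comparisons.
4. Hence a × b = 0 × b = 0 for every value of b. A strong link between genotype and loneliness does not alter this.

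The protocol describes no post-intervention genetic measure, such as expression or methylation, that could give a mediator reading a basis.

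**How often the planned interval would mislead.** A two-arm version of the model was simulated with genotype independent of arm, using a 95% bias-corrected bootstrap interval with 1,000 bootstraps (the protocol's number) and 1,000 simulated trials per setting.

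Inputs from the protocol:
- saliva subsample: 966 / 3 = 322, about 107 per arm, so 2 × 107 = 214 for two arms
- full sample: 2 × 322 = 644 for two arms
- arm effect on outcome: 0.25 SD, the sample-size effect

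Assumptions not in the protocol:
- allele frequency 0.3
- genotype effect b of 0, 0.2 or 0.4 outcome (residual) SD per SD of genotype

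| n (two arms) | b | Mean indirect effect | Interval excludes zero |
|---|---|---|---|
| 214 | 0 | 0.0001 | 0.6% |
| 214 | 0.2 | −0.0003 | 6.7% |
| 214 | 0.4 | 0.0039 | 6.1% |
| 644 | 0 | 0.0000 | 0.7% |
| 644 | 0.2 | −0.0004 | 6.8% |
| 644 | 0.4 | 0.0011 | 5.8% |

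The mean is close to zero throughout. When b = 0 both paths are null and the interval is very conservative. When b is not zero, the interval in effect tests a alone, and the rate is near the nominal 5% or a little above. The Monte Carlo standard error at 5% is √(0.05 × 0.95 / 1000) = 0.7 percentage points. The larger sample does not lower the rate.

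**The mediator list against the rest of the protocol.** Cortisol is a mechanism in the abstract and has four defined indicators in the Biomarkers paragraph under Mediators, but it is absent from the closing list in the analysis section. The list therefore leaves out a variable that could mediate while including variables that cannot.

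**The case against.** No text in the protocol supports a path from arm to genotype. The objections concern how far the point reaches, and several of them stand.

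- **False-positive rate.** A reader might infer that 10, 20 or 50 markers tested at 5% give a 40%, 64% or 92% chance of a spurious mechanism (1 − 0.95^k, independent markers). That formula describes a test of the arm-to-gene path, and the protocol plans to test the indirect effect. At 0.65% per marker the same counts give 1 − 0.9935^k, about 6%, 12% and 28%; at 6.5% per marker, 1 − 0.935^k gives about 49%, 74% and 97%. The marker counts are invented for illustration, and which per-marker rate applies depends on genetic effects the protocol does not state. No family-wise figure should be quoted as the trial's error rate.
- **Genome-wide power.** It is tempting to add that a genome-wide search in about 322 people could find only very large effects. That has no bearing on whether genotype can mediate. The number also rests on an inference: "One third of participants in the sample will be invited to provide saliva samples" comes from the cortisol and CRP paragraph, and the number genotyped is never given.
- **Cortisol.** A reader might infer that cortisol is announced and then not analysed. The analysis text introduces its path models for the proposed mediators generally, and cortisol sits under that heading, so the omission may be only a gap in a list.
- **Moderation.** Nor can it be said that effect modification by genotype will never be examined, because an analysis plan that is not shown may cover it. But that possibility does not excuse the mediator wording, which assigns a named analysis to named variables.
- **Power of the replacement.** An arm-by-score interaction may itself be weakly powered. This is fair, and is why it should be labelled exploratory.

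**Conclusion.** The protocol is wrong as written in treating candidate genes, polygenic scores and SNPs as mediators, and this contradicts its own description of them as dispositions. The true indirect effect through each is zero. That conclusion needs only the order of sampling and allocation and the fact that genotype is inherited.

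The size of the risk is less certain: about 0.6–0.7% per marker unrelated to outcome and about 6–7% per marker related to it, under the assumed allele frequency and effect sizes, with the number of markers unstated.

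The fault is confined to the genetic path models. A reader might infer that the whole mediation analysis fails or that the trial's main result is in doubt. Neither follows: mindfulness, happy or meaningful events and CRP are measured after the intervention and remain legitimate candidates, and the primary Group × Time comparison of loneliness does not use the genetic variables. The point should be corrected, but it ranks below faults that endanger the primary analysis.

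**What to change.** 1. Delete candidate genes, polygenic risk scores and SNPs from the mediator list in the analysis section, and move the Genotyping paragraph out from under Mediators. Amend the abstract's sentence on mechanisms to match.
2. State that the genetic variables will be analysed as baseline effect modifiers, through an arm × genetic score interaction, and label this exploratory. Power is likely to be limited, particularly if only the one-third saliva subsample is genotyped, which is an assumption the protocol should confirm or correct by stating the number genotyped.
3. Keep mindfulness, happy or meaningful events and CRP as mediators, and add the cortisol indices so that the list agrees with the abstract and the Biomarkers paragraph.

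The cost is a few sentences and an interaction model in place of the genetic path models. No new data are needed, so the change is still possible although recruitment has closed.

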### Discussion

Participant recruitment of the study started in 20 April 2022 and completed in 30 April 2023. The project is under the stage of data collection and we estimated to complete data collection in April 2024. The protocol paper has been completed and submitted on 4 April 2023 before completing participant recruitment. However, due to technical problems encountered in submission, the submission of the protocol was delayed.

## Supplement 1. Study Protocol

Although there are a number of interventions that have successfully reduced loneliness in the literature, few focus on older adults as their target despite the fact that a large proportion of older adults report loneliness (1,52). One challenge in delivering any intervention to lonely older adults is that it is difficult to approach them because of their low mobility and sociality. Such challenges become particularly conspicuous during the pandemic. In view of this, we propose the study described in this article to investigate the effectiveness of two telephone-based interventions compared to an active control.

This trial will be the first to test telephone-based interventions in reducing loneliness in older adults in Hong Kong. We will compare the effectiveness of an approach aiming to increase positive and meaningful experiences (i.e., behavioral activation) and an approach aiming to decrease negative experiences (i.e., mindfulness meditation) against an active control group in reducing loneliness. In addition to testing the main effects of the interventions, we will test the behavioral and biological mechanisms underlying the effects.

Telephone-based interventions enable delivery of interventions to people who are difficult to reach because of mobility and/or travel constraints. Such method is particularly beneficial to low-income older adults who live alone and have limited/no internet access during the pandemic. If the method is shown to be successful in Hong Kong, it will facilitate the launch of large-scale community-based interventions in the future.

To summarize, if the interventions are found to be effective, they will provide a scientific understanding on the effectiveness of the two intervention approaches to reduce loneliness. The findings will facilitate the establishment of large-scale interventions to reduce loneliness and promote improved well-being among older adults in Hong Kong.

### **Trial Status**

The current protocol is version 2, 29 September 2023 with the first version completed on 4 April 2023. Recruitment began on the 20st April 2021 and participant recruitment was completed on 30 April 2023. Follow-up of participants will continue until April/May 2024.

### **List of abbreviations**

BA: Behavioral activation

MF: Mindfulness

BF: Befriending

MBSR: Mindfulness-Based Stress Reduction

CRP: C-reactive protein

MAT: Monitor and Acceptance Theory

RCT: Randomized Controlled Trial

Tele-BA: telephone-delivered behavioral activation

Tele-MF: telephone-delivered Mindfulness

Tele-BF: Tele-Befriending

## **Supplement 1. Study Protocol**

470 MoCA: Montreal Cognitive Assessment  
471 FFMQ: Five Facet Mindfulness Questionnaire  
472 SBE: single-base extension  
473 TEI: Treatment Evaluation Inventory  
474 ANOVA: one-way analysis of variance  
475 SPIRIT: Standard Protocol Items—Recommendations for Interventional Trials  
476 CONSORT: Consolidated Standards of Reporting Trials  
477

478 Table 1. SPIRIT schedule of enrolment, interventions, and assessments.

|                                | STUDY PERIOD   |                       |                            |           |           |           |                                                               |                                                                |                                                                |                                                                 |
|--------------------------------|----------------|-----------------------|----------------------------|-----------|-----------|-----------|---------------------------------------------------------------|----------------------------------------------------------------|----------------------------------------------------------------|-----------------------------------------------------------------|
|                                | Enrol-
ment | Allo-
cation       | Post-allocation            |           |           |           |                                                               |                                                                |                                                                |                                                                 |
| TIMEPOINT                      | -1             | Base-
line
(T0) | Intervention period |           |           |           | 4-
week
follow-
up post
Interven-
tion
(T1) | 3-
month
follow-
up post
Interven-
tion
(T2) | 6-
month
follow-
up post
Interven-
tion
(T3) | 12-
month
follow-
up post
Interven-
tion
(T4) |
|                                |                |                       | Week
1                  | Week
2 | Week
3 | Week
4 |                                                               |                                                                |                                                                |                                                                 |
| ENROLMENT:                     |                |                       |                            |           |           |           |                                                               |                                                                |                                                                |                                                                 |
| Eligibility screen             | X              |                       |                            |           |           |           |                                                               |                                                                |                                                                |                                                                 |
| Informed consent               | X              |                       |                            |           |           |           |                                                               |                                                                |                                                                |                                                                 |
| Allocation                     |                | X                     |                            |           |           |           |                                                               |                                                                |                                                                |                                                                 |
| INTERVENTIONS:                 |                |                       |                            |           |           |           |                                                               |                                                                |                                                                |                                                                 |
| Tele-BA                        |                |                       | X                          | X         | X         | X         |                                                               |                                                                |                                                                |                                                                 |
| Tele-MF                        |                |                       | X                          | X         | X         | X         |                                                               |                                                                |                                                                |                                                                 |
| Tele-BF                        |                |                       | X                          | X         | X         | X         |                                                               |                                                                |                                                                |                                                                 |
| ASSESSMENTS:                   |                |                       |                            |           |           |           |                                                               |                                                                |                                                                |                                                                 |
| Socio-demographic
variables |                | X                     |                            |           |           |           |                                                               |                                                                |                                                                |                                                                 |
| Covariates                     |                | X                     |                            |           |           |           | X                                                             |                                                                |                                                                |                                                                 |
| Primary Outcome                |                | X                     |                            |           |           |           | X                                                             | X                                                              | X                                                              | X                                                               |
| Secondary Outcomes             |                | X                     |                            |           |           |           | X                                                             | X                                                              | X                                                              | X                                                               |
| Mediator variables             |                | X                     |                            |           |           |           | X                                                             | X                                                              | X                                                              | X                                                               |

